#### Secondary outcomes

Proportion of participants with a favorable treatment outcome at 48 weeks post-treatment completion.Proportion of participants achieving treatment success at treatment completion (week 40).Proportion of participants experiencing mortality from all causes.Proportion of participants experiencing grade 3 or greater treatment-emergent adverse events (TEAEs) during study treatment and follow-up phases.Proportion of participants experiencing TEAEs of all types.Proportion of participants with a modified favorable treatment outcome at treatment completion and 48 weeks post-treatment completion.Proportion of participants with TB relapses and re-infections during the post-treatment follow-up phase.Proportion of participants harboring *MTB* that develops resistance to BDQ and other drugs included in the regimen.

### Participant timeline {13}

See Table 1.

### Sample size {14}

The primary study null hypothesis posits that the all-oral, BDQ-containing SCR is inferior to that of the all-oral SCR without BDQ. Conversely, the primary study alternative hypothesis posits that the all-oral, BDQ-containing SCR is non-inferior to that of the all-oral SCR without BDQ. Both hypotheses will be tested by measuring the intergroup difference in the proportion of patients achieving favorable treatment outcomes at treatment completion, with results of analysis interpreted using a 15% non-inferiority margin and a 2.5% one-sided significance level.

Under the null hypothesis of inferiority, the favorable treatment outcome rate at treatment completion is assumed to be 85% for the control SCR and 70% for the BDQ-containing regimen. To achieve 80% power in demonstrating the non-inferiority of the BDQ-containing SCR as compared to the control SCR using the abovementioned non-inferiority margin and significance level cutoffs, a sample size of 95 evaluable patients per regimen is required.

Assuming that 10% of randomized patients would not be evaluable for the primary treatment outcome analysis, a total of 212 randomized patients (106/regimen) would be needed.

### Recruitment {15}

Patients who have received recent GeneXpert results indicating resistance are offered counseling sessions and may be considered for inclusion in the screening phase after providing informed consent. To inform the public about the study, news of its initiation is published in local newspapers, and both electronic and printed posters are distributed at each site to recruit participants.

Healthcare staff have established patient-centered care groups to offer consultation, health education, and psychological support throughout the study. On average, we are admitting eight to 10 cases per month at the current rate. Additionally, we have prepared new trial sites in case recruitment progresses slower than planned.

## Assignment of interventions: allocation

### Sequence generation {16a}

Participants who meet the enrollment criteria will be randomly assigned in a 1:1 ratio to the BDQ-containing SCR or the SCR without BDQ. The randomization schedule will be balanced using permuted blocks and stratified by study site and extent of lung cavitation (no cavity or cavity < 2 cm, presence of at least one cavity ≥ 2 cm in one lung only, presence of at least one cavity ≥ 2 cm in both lungs). The randomization sequence is generated by SAS 9.4.

### Concealment mechanism {16b}

The subject randomization schedule will be generated by the randomization statistician and imported into the Interactive Web Response System (IWRS) by the system engineer.

### Implementation {16c}

Randomization is available only to eligible participants who have provided the required randomization information, including stratified factors. The IWRS will then assign a randomization number to participants in sequential order based on the pre-established randomization table. Each randomization number will correspond to a specific group (intervention group or control group). The allocation sequence is prepared by an independent randomization statistician and the investigator of each site will enroll participants, and the interventions will be assigned by IWRS according to the production list.

## Assignment of interventions: blinding

### Who will be blinded {17a}

PROSPECT is an open-label study.

### Procedure for unblinding if needed {17b}

No unblinding procedure is needed for PROSPECT because it is an open-label study.

## Data collection and management

### Plans for assessment and collection of outcomes {18a}

Efficacy assessments included sputum smears, sputum cultures performed using the MGIT 960 system at all sites, DST of isolates derived from *MTB*-positive sputum cultures, and *MTB* genotyping/fingerprinting. Safety assessments will include regular physical examinations, monitoring of AEs, visual acuity testing, and routine blood examinations (e.g., hematology, clinical chemistry, TSH level testing for subjects receiving PTO, urinalysis, and ECGs). All study data will be recorded in source documents and transcribed by study-site personnel from source documents to generate electronic case reports (eCRFs) using an electronic data capture (EDC) system (https://prospect.imeddig.com.). To ensure that recorded data are consistent with original source data, source documents will be mutually agreed upon by the sponsor and investigators at each site before they are made available for direct access.

### Plans to promote participant retention and complete follow-up {18b}

Patients will be educated about the importance of treatment adherence with an emphasis on self-administration of scheduled drugs and completion of clinical follow-up visits. To reduce the chance that participants will be lost to follow-up, attempts will be made to obtain contact information (e.g., home, work, and mobile telephone numbers and email addresses) from each participant and appropriate family members. A participant will not be deemed lost to follow-up until all reasonable efforts have been made by study-site personnel to contact the participant. The following actions must be taken if a participant fails to return to the study site for a required study visit:Study-site personnel must attempt to promptly contact participants to reschedule missed visits. During this communication, they should counsel the participant on the importance of adhering to the assigned visit schedule and ascertain whether the participant wishes to or should continue to participate in the study.Before a participant is deemed lost to follow-up, the investigator or designee must make every reasonable effort to reestablish contact with the participant. Such efforts should include conducting a minimum of three telephone calls, sending emails and/or fax communications, and if warranted, sending a certified letter to the participant’s last known mailing address (or local equivalent method). Every attempt to make contact should be recorded in the participant’s medical records. In the event that the participant cannot be contacted, the participant will be officially categorized as having voluntarily withdrawn from the study.

### Data management {19}

All eCRFs will be designed and generated by the sponsor/designee in accordance with protocols and requirements as stipulated by the Code of Federal Regulations Title 21, Part 11 (21 CFR Part 11). To maintain data integrity, all eCRF entries, corrections, and alterations will be exclusively carried out by the investigator or authorized study-site personnel who have received relevant training in accordance with eCRF Completion and Data Entry Guidelines. The investigator assumes the vital responsibility of verifying the accuracy and correctness of all eCRF data entries. Following participant visits, eCFRs will be completed as soon as possible to ensure that completed forms are readily accessible for review during the subsequent scheduled monitoring visit. For consistency and standardized reporting, investigators will record adverse events as coded terms derived verbatim from the Medical Dictionary for Regulatory Activities (MedDRA).

The data management team (DMT) will conduct regular reviews to ensure data completeness and accuracy in accordance with the Data Management Plan and Data Management Quality Control Plan. The EDC system will perform logical checks automatically after data entry using a built-in algorithm that aligns with the data validation plan (DVP). Manual data checks will be performed monthly and may increase in frequency with rising data input and database locking rates. Both logical and manual review queries will be generated using the EDC system to request clarifications for inaccurate or incomplete data. Database locking will adhere to preestablished rules as indicated in the corresponding standard operating procedure (SOP).

### Confidentiality {27}

The collection, sharing, and processing of personal data from participants enrolled in this study are limited to those data that are necessary to fulfill study objectives. Such data must be collected and processed with adequate precautions to ensure confidentiality and compliance with applicable data privacy protection laws and regulations. Appropriate technical and organizational measures will be taken to ensure that participant personal data will not be subject to unauthorized disclosures or access, accidental or unlawful destruction, or accidental loss or alteration. Sponsor/designee personnel whose responsibilities require access to personal data will be required to agree to maintain patient confidentiality. A unique trial number will be assigned to each participant.

### Plans for collection, laboratory evaluation, and storage of biological specimens for genetic or molecular analysis in this trial/future use {33}

Three sputum samples will be collected from each participant at pre-scheduled visits, as detailed in Table 1; these samples will include one sample taken at night, one collected early the next morning, and one coached spot expectoration sample. While awaiting receipt of phenotypic DST results, participant *MTB* isolates will be screened for RMP resistance using GeneXpert, while other molecular DST methods will be used to screen for FQs resistance and INH resistance-associated *inhA* and *katG* mutations. Participants harboring *MTB* with susceptibility to RMP and INH, FQ resistance, or *inhA* mutation-induced INH resistance will be excluded from the trial. Participants harboring *MTB* with RMP resistance, INH sensitivity, or high-level INH resistance due to *KatG* mutations and FQs susceptibility, as confirmed using molecular methods, may be enrolled in the study while awaiting phenotypic DST results.

MGIT-based DST will be performed on cultures derived from specimens obtained at baseline, during treatment, and during the follow-up period. Phenotypic DST will be performed during the screening phase to detect resistance to RMP, INH, LFX, LZD, CFZ, PTO, and BDQ. If sputum cultures obtained at screening test positive for drug resistance within 1 month prior to the date of administration of the first dose of the study regimen, the culture obtained at screening may serve as the baseline culture. Post-baseline cultures of specimens collected from participants during or after week 16 of treatment that test positive for *MTB* will be stored until assayed via DST. DST will also be performed on any *MTB*-positive culture derived from specimens obtained during the follow-up period. Cultures obtained from specimens collected during the follow-up period from participants with treatment success who later revert to *MTB*-positive status (as indicated by culture conversion or disease relapse) will be genotyped, with paired *MTB*-positive isolates used for genotypic analysis.

## Statistical methods

### Statistical methods for primary and secondary outcomes {20a}

Primary efficacy analysis will be conducted using a stratified analysis method, whereby the risk difference for each stratum is determined using Cochran Mantel–Haenszel weights. Using this analysis method, differences in favorable treatment outcome rates at the end of treatment between the control SCR and the BDQ-containing SCR will be estimated along with corresponding 95% confidence intervals (CIs) and *p*-values. Thereafter, intergroup rate differences will be stratified according to study site and lung cavitation status. To meet pre-specified non-inferiority criteria, the upper bound of the 95% CI of the difference in the proportion of the favorable treatment outcome must be < 15%. Primary efficacy analysis will be conducted using the efficacy analysis dataset, as defined in Table 3. For the secondary outcomes, point estimates and CI values will be calculated to estimate differences in proportions between the BDQ-containing SCR and the control SCR without BDQ using the same stratified analysis as for the primary endpoint.

**Table 3 Tab3:** Populations set for analysis

Population	Description
Intent-to-treat (ITT)	All randomized participants
Safety analysis set	All randomized participants who consume at least 1 dose of the study intervention
Modified ITT	Subset of the ITT with proper diagnosis, including all randomized participants with a positive *MTB* culture result at screening or randomization; excludes participants who provided isolates prior to randomization that were subsequently found to harbor RIF-susceptible *MTB* or participants who provided isolates prior to randomization that were subsequently found to be resistant to drugs in the regimens (including low-level INH resistance), as revealed by phenotypic DST results
Efficacy analysis set	All enrolled participants with confirmed pulmonary MDR-TB and a positive *MTB* culture at screening or baseline who were not withdrawn from the study because they harbored *MTB* with baseline resistance to prescribed drugs and consumed at least 1 dose of study treatment

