**Discussion:**

PROSPECT aims to assess the safety and efficacy of a BDQ-containing SCR MDR-TB treatment at seventeen sites across China, while also providing high-quality data to guide SCRs administration under the direction of the China National Tuberculosis Program for MDR-TB. Additionally, PROSPECT will explore the potential benefits of extending the administration of the 9-month BDQ-containing SCR for participants without sputum conversion by week 16.

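### Site-by-cavitation strata (on the natural reading 51 cells for about 190 patients) are too fine for the primary risk difference: some patients get zero weight and a few points of power are lost

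*Protocol article*

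**What the plan says.** Statistical methods for primary and secondary outcomes {20a} sets the primary analysis as a Mantel-Haenszel weighted difference in favourable outcome rates with a 95% confidence interval. Non-inferiority is declared if the upper bound is below 15%. The strata are given by the statement that "intergroup rate differences will be stratified according to study site and lung cavitation status". Secondary outcomes are to be analysed "using the same stratified analysis as for the primary endpoint".

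Sequence generation {16a} uses the same factors for randomisation, in permuted blocks "stratified by study site and extent of lung cavitation", with three cavitation levels. The abstract places the trial "at seventeen sites across China". Recruitment {15} adds that further sites have been prepared in case enrolment is slow.

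Sample size {14} uses "a 15% non-inferiority margin and a 2.5% one-sided significance level" and concludes that "a sample size of 95 evaluable patients per regimen is required". None of these sections gives a block size, a rule for pooling small sites or a variance estimator for the stratified difference.

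**The concern.** Crossing 17 sites with three cavitation levels leaves fewer than two evaluable patients per arm in the average cell. Two things follow.

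- A cell that holds only one arm has zero Mantel-Haenszel weight. Its patients are randomised and followed up but do not enter the primary estimate. The sample size was calculated without strata and makes no allowance for this.
- In very small cells the choice of variance formula matters. A formula that adds up binomial variances cell by cell gives an interval that is too short, and the non-inferiority claim rests on one bound of that interval.

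Adding sites would thin the cells further.

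**Working it through.** **Inputs from the article.** Margin 15 points; one-sided level 2.5%; power 80%; 95 evaluable per arm (190 in all); 10% not evaluable; 212 randomised 1:1; 17 sites; three cavitation levels. Under the null, "the favorable treatment outcome rate at treatment completion is assumed to be 85% for the control SCR and 70% for the BDQ-containing regimen". The rate under the alternative is not stated; 85% in both arms is assumed.

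**The plan's own figure.** The Farrington-Manning score formula has restricted null rates of 0.899 and 0.749:

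n = [1.96·√(0.899·0.101 + 0.749·0.251) + 0.8416·√(2·0.85·0.15)]² / 0.15² = (1.035 + 0.425)² / 0.0225 ≈ 94.7

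With unrounded rates it is 94.8, so 95 per arm. Then 95/0.9 = 105.6, so 106 per arm and 212 in total. The stated figures reproduce, as an unstratified calculation.

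**Cell size.** 17 × 3 = 51; 190/51 = 3.7 per cell; 3.7/2 ≈ 1.9 per arm.

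**Weights.** Each cell has weight w = n₁n₀/(n₁+n₀). A 3-versus-0 cell has w = 0.

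**Power by hand.** Unstratified SE = √(2·0.85·0.15/95) = 0.0518. The information kept, Σw divided by its unstratified value, was simulated at 0.91-0.92 for blocks of 2 and 0.86-0.89 for blocks of 4 to 6. At 0.92 the SE is 0.0518/√0.92 = 0.0540; at 0.86 it is 0.0518/√0.86 = 0.0559. Power ≈ Φ(0.15/SE − 1.96):

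- unstratified: Φ(0.94) ≈ 83%
- 0.92 kept: Φ(0.82) ≈ 79%
- 0.86 kept: Φ(0.72) ≈ 77%

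**Variance.** The expected cell-wise estimate p̂(1−p̂)/n equals the true p(1−p)/n times (n−1)/n. It is halved at n = 2 and zero at n = 1. In a 1-versus-1 cell, w = 0.5 and the true contribution at equal rates is 0.25 × 2·0.85·0.15 = 0.25 × 0.255. The cell-wise formula contributes 0. The Sato formula contributes 0.25 whenever the pair is discordant, which has probability 0.255, so its expectation is right.

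**Simulation.** 212 patients, permuted blocks within 51 cells, 190 evaluable at random, 3,000 to 8,000 replicates per scenario. Site sizes, cavitation mix (for example 50/30/20%), block size and prognostic effects are assumptions. Results for blocks of 4:

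| Site sizes | Site and cavitation prognostic? | Patients with zero weight | Power, 51 cells, Sato | Power, 3 strata, Sato | Type I error, 51 cells, Sato | Type I error, 51 cells, cell-wise |
|---|---|---|---|---|---|---|
| equal | no | 12.6 | 78.7% | 82.9% | 2.7% | 7.8% |
| moderately uneven | no | 14.0 | 77.5% | 81.7% | 2.8% | 7.3% |
| very uneven | no | 16.8 | 78.3% | 83.2% | 2.5% | 5.6% |
| equal | yes | 12.6 | 85.2% | 87.1% | 3.0% | 8.5% |
| moderately uneven | yes | 14.0 | 84.7% | 86.9% | 2.9% | 8.0% |
| very uneven | yes | 16.7 | 84.0% | 86.9% | 2.8% | 6.8% |

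The power lost against three strata is 4 to 5 points without prognostic effects and 2 to 3 points with them. Over all scenarios and blocks of 2 to 6, about 7 to 19 patients get zero weight. Without prognostic effects, Sato power with 51 cells is 77-81%, against 82-84% with three strata.

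With cell-wise variances and equal rates, the mean SE is 0.037-0.044 against a true SD of 0.053-0.056. Coverage of the 95% interval is 82-89% and the one-sided type I error is 5.4-9.1%. With Sato, coverage is 94-96%. At 3,000 replicates the simulation error of a 2.5% rate is √(0.025·0.975/3000) ≈ 0.3 points, so the Sato type I errors lie close to nominal.

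**At the decision bound.** With SE 0.054 non-inferiority is met if the observed deficit is below 15 − 1.96·5.4 = 4.4 points. With SE 0.040 it is met below 15 − 1.96·4.0 = 7.2 points. Between the two, the formula alone decides.

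**The case against.** Analysing by the randomisation factors is conventional, and the precision lost is small. Power with a valid variance stays close to the planned 80%, and above it if the factors are prognostic. Zero weight for some cells has not been shown to cause bias. A variance formula and a pooling rule are details that an article commonly leaves to the analysis plan, which is not shown. All of this stands and limits the point to a modest one.

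Three stronger readings are tempting and are not supported.

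- A reader might infer that the planned interval is too narrow and the type I error inflated. The article chooses no variance estimator, and with Sato the 51-cell interval holds its level. The inflation arises only under one possible choice.
- A reader might infer that the sample size is wrong. It reproduces.
- A reader might infer that rare secondary outcomes, such as death or relapse, are badly affected. The same strata do apply to them, but no calculation was made.

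The text also does not say outright that the two factors are crossed, and the sentence that introduces the strata leaves the order of steps unclear. Crossing is the natural reading of a risk difference per stratum on both factors. If it is not meant, the primary strata still need to be stated.

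**Conclusion.** The point holds as a low-cost improvement, not as an error that invalidates the analysis. The stratification stated for the primary analysis is finer than 190 evaluable patients can support. It gives no weight to about 7-19 of them (4-10%). Without prognostic effects, power is about 77-81% rather than 82-84%; with them, 84-85% rather than about 87%. The validity of the interval then turns on the variance estimator, sound with Sato and about 5-9% one-sided type I error with cell-wise binomial variances. The sizes rest on the crossed reading, 85% favourable in both arms for power, non-evaluability at random, and the assumed site sizes, cavitation mixes and block sizes.

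**What to change.** In {20a}, state that the Mantel-Haenszel strata for the primary and secondary analyses are the three cavitation levels, or cavitation by a few pooled site groups defined before database lock. Name a Sato or stratified Miettinen-Nurminen interval. Keep the full site-by-cavitation stratification, with the same kind of variance, as a sensitivity analysis. In the simulations, three cavitation strata lose no patients and have a type I error close to nominal.

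This takes a sentence or two and leaves randomisation, sample size and conduct unchanged. The drawback is that the primary analysis no longer conditions on each individual site, although site is a randomisation factor; pooled site groups and the sensitivity analysis recover part of that. If the 51 cells are kept, naming a variance that is valid for sparse data is enough for validity, and the price is the few points of power.

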#### Explanation for the choice of comparators {6b}

The SCR without BDQ consists of LFX (40 weeks), LZD (at least 24 weeks), CS (40 weeks), CFZ (40 weeks), pyrazinamide (PZA) (40 weeks), and PTO (initial 16 weeks) and is designed to serve as a comparator under self-administration trained by appointed nurses The control arm treatment is modified by removing high-dose INH and injectable KM, then regimen efficacy is enhanced by adding LZD and CS based on Regimen B of STREAM trial.

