#### Intervention descriptions {11a}

Experimental arm participants will be instructed to self-administer the assigned dose of BDQ in combination with the following four drugs: LFX (40 weeks), LZD (at least 24 weeks), CS (40 weeks), and CFZ (40 weeks). During the study treatment phase, these participants will receive an all-oral SCR consisting of 24 weeks of BDQ in combination with 40 weeks of other allocated TB treatment drugs (except for LZD, which will be administered for at least 24 weeks). If a participant is still sputum culture-positive for *MTB* by week 16, BDQ treatment will be extended from 24 to 40 weeks.

Detailed information for drugs administered to trial participants is provided in Table 2.

**Table 2 Tab2:** Detailed information for the individual drug of each arm in the PROSPECT study

Drug	BDQ	LFX	LZD	CS	CFZ	PZA	PTO
BDQ-containing regimen (duration [weeks])	X (24 to 40)^a^	X (40)	X (≥ 24)	X (40)	X (40)		
Non-BDQ-containing regimen (duration [weeks])	NA	X (40)	X (≥ 24)	X (40)	X (40)	X (40)	X (First 16)
Dosage formulation	Uncoated tablet	Film-coated tablet	Tablet	Capsule	Capsule	Tablet	Enteric-coated tablet
Unit dose strength	100 mg	100 mg and 500 mg	600 mg	250 mg	50 mg	250 mg	100 mg
Dose regimen	400 mg once daily for the first 2 weeks, 200 mg 3 times per week (with at least 48 h between doses) for the remaining weeks (i.e., 22 weeks or 38 weeks in case bedaquiline treatment is extended to 40 weeks)	30–35 kg: 600 mg daily 36–55 kg: 750 mg daily > 55 kg: 1000 mg daily	600 mg daily	30–45 kg: 500 mg daily > 45 kg: 750 mg daily	100 mg daily	30–35 kg: 1000 mg daily 36–70 kg: 1500 mg daily > 70 kg: 2000 mg daily	30–45 kg: 500 mg daily 46–70 kg: 600 mg daily > 70 kg: 800 mg daily

^a^If a participant is still sputum culture-positive for *MTB* by week 16, BDQ treatment will be extended from 24 to 40 weeks

*NA*, not available

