#### Criteria for discontinuing or modifying allocated interventions {11b}

A participant’s study intervention must be discontinued if:The participant withdraws consent to receive the study intervention.The investigator believes that for safety or tolerability reasons it is in the best interest of the participant to discontinue the study intervention. Individual drug substitutions within the study intervention regimen may be considered if clinically indicated at the discretion of the investigator. Administration of single-drug substitutions will not be viewed as an unfavorable treatment outcome criterion if limited to substitutions of non-group A drugs (except DLM) as per the 2020 WHO MDR-TB treatment guidelines.The participant becomes pregnant.Unacceptable toxicity.The patient experiences:Aminotransferase elevations with total bilirubin elevations to levels of ≥ twofold the ULNAminotransferase elevations to levels that are ≥ eightfold greater than the ULNAminotransferase elevations to levels that are ≥ fivefold greater than the ULN and persist for more than 2 weeks.If the patient experiences a QTcF interval > 500 ms (as confirmed by repeat ECG) and/or clinically significant ventricular arrhythmia.Noncompliance with study drug administration.Any participant not meeting eligibility criteria as specified in the “Eligibility criteria” section.

A participant will be withdrawn from the study for any of the following reasons:If phenotypic DST results from a screening sample become available post-baseline confirming resistance at the start of the study to any of the drugs in the assigned regimen except BDQ, in which case the patient will be treated according to local treatment protocols after withdrawal from the study.Lost to follow-up.Withdrawal of consent.Death.

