### Methods in analysis to handle protocol non-adherence and any statistical methods to handle missing data {20c}

We plan to perform an intention-to-treat analysis and will address missed data by analyzing available data or by employing multiple imputation techniques.

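### The primary analysis set removes participants with baseline prothionamide resistance from the control arm but keeps them in the bedaquiline arm

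*Protocol article*

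**What the plan says.** Section {20a} of the protocol article names the primary population: "Primary efficacy analysis will be conducted using the efficacy analysis dataset, as defined in Table 3". Table 3 restricts that set to enrolled participants with confirmed pulmonary MDR-TB and a positive culture who were not withdrawn for harbouring an isolate "with baseline resistance to prescribed drugs and consumed at least 1 dose of study treatment".

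Section {11b} gives the withdrawal rule. A participant leaves the study if phenotypic drug susceptibility testing (DST) on a screening sample is reported after baseline "confirming resistance at the start of the study to any of the drugs in the assigned regimen except BDQ".

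The regimens are in {11a} and {6b}. The experimental arm takes "BDQ in combination with the following four drugs: LFX (40 weeks), LZD (at least 24 weeks), CS (40 weeks), and CFZ (40 weeks"). The control arm takes the same four companion drugs plus "pyrazinamide (PZA) (40 weeks), and PTO (initial 16 weeks").

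Section {33} lists the panel: "Phenotypic DST will be performed during the screening phase to detect resistance to RMP, INH, LFX, LZD, CFZ, PTO, and BDQ". It also lets participants enrol on molecular results while phenotypic results are pending.

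Two other statements bear on the point. The modified ITT set in Table 3 excludes isolates "subsequently found to be resistant to drugs in the regimens (including low-level INH resistance"), in the plural and without reference to assignment. Section {20c} says "We plan to perform an intention-to-treat analysis", without calling it primary.

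**The concern.** A baseline isolate is a pre-randomisation characteristic, so excluding on it is legitimate in principle, provided the same rule applies in both arms. Here the list of disqualifying drugs depends on allocation. Of two participants with identical PTO-resistant isolates, one is dropped and the other analysed, purely because of the arm drawn. The two arms of the primary comparison are then selected differently, and the estimate no longer rests on randomisation alone. The article itself names and defines this population, so the point is not a detail left to an analysis plan.

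**Working it through.** **Which resistance removes whom**

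| Drug | In BDQ arm | In control arm | On screening panel | Removal under {11b} |
|---|---|---|---|---|
| Levofloxacin, linezolid, clofazimine | yes | yes | yes | both arms |
| Cycloserine | yes | yes | no | both arms, if tested |
| PTO | no | yes | yes | control only |
| Pyrazinamide | no | yes | no | control only, if tested |
| BDQ | yes | no | yes | exempt |

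The only drug peculiar to the experimental arm is exempt, so every arm-specific removal falls on control. PTO is the drug through which the listed panel makes this happen.

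**The plan's own figure.** Inputs from {14}: control rate 85%, margin 15 points, one-sided 2.5%, power 80%. The article does not state the alternative; 85% in both arms is assumed. The Farrington-Manning formula uses null rates from the restricted likelihood, 0.749 and 0.899:

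- null variance: 0.749 × 0.251 + 0.899 × 0.101 ≈ 0.279
- alternative variance: 2 × 0.85 × 0.15 = 0.255
- n = (1.960 × √0.279 + 0.842 × √0.255)² / 0.15² = 94.8, so 95 per arm
- 95 / 0.9 = 105.6, so 106 per arm and 212 in total

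Both stated figures are reproduced.

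**Bias.** Let r be the share of participants whose isolates resist PTO but no shared drug, and d the deficit in their favourable rate against other participants in the BDQ arm. Neither is in the article, so both are assumptions. If the whole-arm rate is 85% in both arms, control after removal has 85% + r × d and the BDQ arm stays at 85%. Control minus BDQ is too high by r × d:

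- r = 5%: 0 at d = 0; 0.5, 1.0 and 1.5 points at d = 10, 20 and 30
- r = 10%: 0 at d = 0; 1, 2 and 3 points
- r = 20%: 0 at d = 0; 2, 4 and 6 points

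Control-only removals would be about 106 × r: 5, 11 and 21 participants.

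**Power under true equality.** Power = Φ[(0.15 − r × d − 1.96 × SE₀) / SE₁], where SE₀ comes from the restricted null rates and SE₁ from the assumed rates. The BDQ arm has 106 × 0.9 = 95.4 and control 95.4 × (1 − r). With r = 0 this gives 80.3%.

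| r | d = 0 | d = 10 | d = 20 | d = 30 |
|---|---|---|---|---|
| 5% | 79.7% | 77.4% | 75.0% | 72.5% |
| 10% | 79.0% | 74.4% | 69.2% | 63.4% |
| 20% | 77.5% | 67.8% | 56.1% | 43.2% |

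If instead the retained control rate is held at 85% and the BDQ arm's rate falls by r × d, the figures at d = 20 are 73.2% (r = 5%) and 65.3% (r = 10%).

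**Would plain ITT cure it?** Section {12} counts treatment discontinuation as unfavourable. If DST-withdrawn control participants are scored that way, the control rate falls by about r × 85%: 0.05 × 85 = 4.25 points at r = 5%, and 8.5 points at r = 10%. The difference then moves toward BDQ. The same arm-dependent rule thus pushes the two analyses in opposite directions.

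**The case against.** The strongest reply is that the effect may be negligible and is in any case conservative. PTO is not in the experimental regimen, so PTO resistance cannot weaken that regimen directly. It could matter only as a prognostic marker, and nothing in the article says it is one. With d = 0 there is no bias and power stays at 77.5–79.7% for r = 5–20%. The share r is also lowered by design. The background section links the inhA mutation to PTO cross-resistance, inhA carriers are excluded before randomisation, and so is previously documented phenotypic resistance to a regimen drug. The r = 20% row is therefore an extreme. If d is positive, the bias makes non-inferiority harder to show. All of this stands, and it limits the severity. It does not remove the asymmetry.

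A reader might also infer more than the article supports:

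- That the BDQ arm keeps everyone. It does not: levofloxacin, linezolid and clofazimine resistance remove participants from both arms.
- That pyrazinamide resistance adds removals. Pyrazinamide is control-only, but it is not on the listed panel.
- That several populations compete for the primary role. Section {20a} names one; {20c} only needs aligning with it.
- That the one-dose condition is part of this fault. Its wording is the same for both arms.
- That no outcomes are collected after DST withdrawal. Section {11b} withdraws these participants from the study, while {30} continues assessments for those who stop the intervention for any reason. How the two fit is unclear, but the article does not say that follow-up ends.

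**Conclusion.** The point holds for PTO. Under {11b}, {6b}, {11a} and {33} read together, the primary set is selected differently by arm, and no selection in the opposite direction offsets it. The size cannot be fixed from the article. On the assumed ranges it is nil if PTO resistance is not prognostic, and about 0.5–3 points of the 15-point margin for r = 5–10% and d = 10–30. For d ≥ 0 the consequence is lost power and a harder test for BDQ. The stronger reading, that the rule inflates the chance of a false non-inferiority claim in the primary analysis, is not supported. This is something to correct before analysis, not a fatal flaw. Whether the clinical withdrawal rule is right is not judged here.

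**What to change.** 1. In Table 3, replace the condition based on withdrawal and prescribed drugs with one based only on pre-randomisation isolates. Use a single drug list, applied to every randomised participant whatever the arm and whether or not withdrawn. The modified ITT wording is a ready template once it is made explicitly arm-neutral, with one decision on BDQ resistance for both arms.
2. Report ITT beside it as a sensitivity analysis, and state how DST-withdrawn participants are scored. Do not require ITT to agree: while arm-dependent withdrawals count as unfavourable, it leans toward BDQ.
3. Reconcile {11b} with {30} so that outcomes are sought for DST-withdrawn participants, and align the ITT sentence in {20c} with {20a}.

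The set can be built from DST results already planned, so no new participants are needed. The cost is a slightly smaller BDQ arm in the primary set and continued follow-up of a few participants. With d = 0, power under the symmetric rule is 78.2% at r = 5% and 75.9% at r = 10%, against 79.7% and 79.0% now. That loss disappears once such participants do moderately worse: at r = 10% and d = 10 the present rule already gives only 74.4%.
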